**B. Background for the Study**

Recent research has demonstrated that placebo treatment can have significant impacts for a wide variety of symptoms (Finiss et al., 2010). Unfortunately, in the traditional understanding response to placebos requires deception. This may cause problems with respect to patient-healthcare provider relationship and ethical difficulties. In contrast to this classic view recent research has demonstrated that placebos may work even without concealment. For example, Kaptchuk et al. (2010) conducted a randomized controlled trail including patients with irritable bowel syndrome. Half of the patiens received placebos without deception, the other half served as a control group. The authors found significantly higher mean global improvement scores, reduced symptom severity, and better quality of life scores for the open-placebo group. Similar results have been reported, for example, for patients with major depression (Kelley et al., 2012) and ADHD (Sandler et al., 2008).

Our previous study has demonstrated that open-label placebos also improve

symptoms in patients with allergic rhinitis (Schaefer et al., 2016). However, this pilot study was based on only few patients. Thus, we here want to replicate the results in a larger sample.

Furthermore, the mechanism of open-label placebo effects remains unclear. Are open-label placebo effects based on bottom-up mechanisms, such as classical conditioning? Or are they linked to raised expectancies about the positive effects of placebos in general, hence representing top-down effects? The latter may be related to the detailed information on the power of placebo effects. This information is included in nearly all open-label placebo studies. In order to disentangle top-down and bottom-up effects, we aim to manipulate this information: Half of the participants will be informed about the power of placebos, the other half not.

We expect to replicate the previous findings that open-label placebos improve allergic symptoms more than in a control group with comparable patient-healthcare provider relationships. Furthermore, we assume that the open-label placebo effect is independent of the information how powerful placebos are, thereby suggesting a bottom-up effect.

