**E. Description of Research Protocol**

Overview: This study aims to test whether non-deceptive administration of placebo in patients with allergic rhinitis will be superior to a control group, and if this effect is independent of detailed information on positive effects of placebos.

Design: 60 patients with allergic rhinitis will be randomized to a two-week course of either non-deceptive placebo pill with detailed information on positive effects of placebos, of non-deceptive placebo pill without detailed information on positive effects of placebos, of no treatment plus usual care with detailed information on positive effects of placebos, and of no treatment plus usual care without detailed information on positive effects of placebos. All groups will receive the same amount of time with the practioner. Participants will be assessed at baseline and at the end of the two weeks.

Design and intervention:

Description of the open-label placebo treatment arms:

After signing the informed consent the patients will be assessed with respect to their allergic symptoms and quality of life. They will be told to note their allergic complaints at the end of each day in an allergic diary. Then they will receive 28 placebos in a white box, labeled with the logo of the university and the following information “Placebo pills (28), take one in the morning and one before night, for 14 days”

Description of the no treatment usual care control arms:

This control group will be treated as the open-placebo group, but do not receive any placebos. The purpose of this control group is to match for time with practioner and to assess general improvements of allergic symptoms due to changes in weather (pollen) conditions.

Description of the detailed information on placebo arms:

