**F. Data Analysis**

Outcome Measures: Two outcome measures will be used at baseline and endpoint of this study:

Allergic symptoms questionnaire:

Participants will be asked to assess their allergic symptoms by using a questionnaire describing different symptoms (itching, prickling, or burning feelings in the nose; constipated or running nose; impaired sense of smell or taste; sneezing fits; feeling like having a cold; itching or irritated skin; eczema on the skin; itching, burning or red eyes; billowed eyelids; itching, prickling or scratching feelings in the throat; sore throat; burning feeling or mucus in the mouth or throat; billowed mucosa; breathlessness; cough; headaches; feelings of exhaustion; lack of concentration; tiredness; disorders of the gastrointestinal tract). The patients will indicate their response on a seven-point scale ranging from ‘never’ (1) to ‘always’ (7). For further analysis we will calculate a composite score including all symptoms (see Schaefer et al., 2016). This is the primary outcome parameter.

Quality of Life (SF36): The SF-36 is a German version of the health survey developed by Ware and Sherbourne (1992) in order to examine subjective well-being and quality of life. This instrument assesses the quality of life with respect to the perception of the health both for patients and healthy people. It includes one multi-item scale that assesses different health concepts such as limitations in physical activities because of health problems, limitations in social activities because of physical or emotional problems, limitations in usual role activities because of physical health problems, bodily pain, general mental health (psychological distress and well-being), limitations in usual role activities because of emotional problems, vitality (energy and fatigue), and general health perceptions.

Planned Statistical Analyses

We will conduct analyses of variance (ANOVA) with three factors (time, placebos, information on the power of placebos) for allergic symptoms as well as for quality of life scores. In addition, we will test if baseline scores are different. All tests will be two-tailed with alpha set at .05.

Statistical Power

Based on effect sizes of our previous study (Schaefer et al., 2016), we will need 104 participants for an alpha set at .05. However, given that this is a pilot study and data collection is limited due to weather (pollen) conditions, we aim to include 60 patients in this study.

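### The protocol states a need for 104 participants and plans 60 without saying what 104 was powered for or what power 60 gives; for the no-interaction hypothesis that power is low

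*Protocol*

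**What the plan says.** The Statistical Power paragraph in section F of the Protocol opens with "Based on effect sizes of our previous study" and continues "we will need 104 participants for an alpha set at .05". The next sentence cites pilot status and the pollen season, and sets the actual target: "we aim to include 60 patients in this study". Section E has the same total, "60 patients with allergic rhinitis will be randomized to a two-week course of either" one of four arms, formed by crossing placebo (yes/no) with information about placebo effects (yes/no).

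The planned analysis is an ANOVA with factors for time, placebo and information, and "All tests will be two-tailed with alpha set at .05".

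The aims are those of a replication. Sections A and C say so. Section B calls the earlier study the pilot, notes that it had few patients, and goes on: "Thus, we here want to replicate the results in a larger sample". Section D sets two hypotheses: open-label placebo is superior to the control, and information does not interact with that effect.

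**The concern.** A sample size tied only to an alpha cannot be checked. It also needs an effect size, a power and a contrast. The three-factor ANOVA offers several candidates for the contrast: the pooled placebo effect, placebo versus control within one information level, or the interaction. The effect sizes are attributed to the previous study, but no number is given.

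The plan then misses its own figure by 44 patients (44/104 = 42%) and does not say what power is left. Part of the stated reason is that this is a pilot, although the study is introduced as the larger replication of one. If both labels stand, a positive result can be read as a replication and a null result set aside as a pilot, and the choice can be made after the data are known.

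The second hypothesis predicts the absence of an effect. Low power makes a non-significant interaction likely whether or not the hypothesis is true, and section B would take independence as pointing to a bottom-up mechanism.

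**Working it through.** **Inputs from the Protocol.** 104 said to be needed and 60 planned (section F, Statistical Power); four arms in a 2×2 layout (section E); two-sided alpha 0.05 (section F).

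**Assumptions, because the Protocol gives no figure.** Equal allocation, so 15 per cell and 30 versus 30 on each factor at 60. Target power behind 104 of 80%, 90% or 95%. Effects in units of the within-cell SD of the change from baseline. No dropout, except where shown.

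**Can 104 be reproduced?** Not forward, because effect size, power and contrast are all missing. It can only be solved backwards. Power comes from the noncentral t distribution, with noncentrality d × √(n/2) for n per side.

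*Reading 1: 104 is 52 versus 52 on the pooled placebo effect.* At 80% power with 100 df the noncentrality must be 2.829, so d = 2.829/√26 = 0.555. With 30 versus 30 it becomes 0.555 × √15 = 2.149. With 56 df (critical value 2.003) the power is 56.0%.

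*Reading 2: 104 is 26 per cell, sized for a contrast of two cells.* At 80% power with 50 df the noncentrality is 2.857, so d = 2.857/√13 = 0.792. With 15 versus 15 it becomes 0.792 × √7.5 = 2.170; with 28 df the power is 55.4%. If the placebo effect is equally large at both information levels, the pooled 30 versus 30 test has 0.792 × √15 = 3.069; with 56 df the power is 85.4%.

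| Assumed target behind 104 | Reading 1: d | Pooled effect at 60 | Reading 2: d | Two-cell contrast at 60 | Pooled effect at 60 |
|---|---|---|---|---|---|
| 80% | 0.555 | 56% | 0.792 | 55% | 85% |
| 90% | 0.642 | 69% | 0.917 | 68% | 94% |
| 95% | 0.714 | 78% | 1.020 | 77% | 97% |

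**Sensitivity, Reading 1 at 80%.** With 54 analysed (10% loss) power is 52%; with 48 (20% loss) it is 47%. If 104 came from a one-sided calculation at 80%, the planned two-sided test has 46% at 60. If it came from a four-group omnibus F test at 80%, that test has 53% at 60.

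**What 60 can detect, whatever 104 meant.** For 80% power with 56 df the noncentrality must be 2.851.

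- Pooled placebo effect: 2.851/√15 = 0.74 SD.
- Interaction (difference D between the two simple placebo effects): its standard error is √(4/15) = 0.516 SD, so the detectable D is 2.851 × 0.516 = 1.47 SD.
- Power for D = 0.55 SD: noncentrality 0.55/0.516 = 1.07, power 18%.
- Power for D = 0.8 SD: noncentrality 0.8/0.516 = 1.55, power 33%.
- Half-width of the 95% confidence interval for D: 2.003 × 0.516 = 1.03 SD.

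The half-width shows what a null interaction would leave open. Suppose the estimated D is exactly zero and the average placebo effect is 0.555 SD. The interval still reaches D = 1.03, which corresponds to simple effects of 0.555 + 0.517 = 1.07 SD at one information level and 0.555 − 0.517 = 0.04 SD at the other.

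**The case against.** The shortfall is not hidden. The paragraph gives both numbers and two reasons, and the pollen season is a genuine feasibility limit that does not depend on the pilot label. Readers know that 60 is below the calculated requirement; what they lack is the size of the loss. This stands.

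A reader might infer that the trial has only 56% power. The Protocol does not support that as a single figure. It needs an 80% target and a pooled 52 versus 52 sizing, and neither is stated. If 104 was 26 per cell, the pooled placebo effect has 85% to 97% at 60, which is adequate for the first hypothesis. This also stands.

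A reader might also infer that 104 was miscalculated. No calculation is shown to be wrong; the inputs are absent and the source study is not at hand. Nor does planning 60 contradict the wish for a larger sample, since section B says the earlier study had few patients and gives no number. The conflict is between pilot status and the replication aim.

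None of this answers the interaction point, which does not depend on how 104 was derived.

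**Conclusion.** The concern holds as a defect of justification and interpretation; no arithmetic error is shown. The Protocol misses a size it states for itself, gives no basis for checking that size, gives no power for the trial it will run, and assigns the trial two statuses.

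Under the two sizing readings, with equal allocation, no dropout and a target of 80% to 95%, power at 60 for the pooled placebo effect lies anywhere from 56% to 97%. The width of that range reflects what the paragraph leaves out. It is not a bound, since dropout or a one-sided derivation would lower the bottom end.

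The firmer conclusion concerns the second hypothesis. With a detectable difference of about 1.47 SD and about 18% power for one of 0.55 SD (an illustrative size, close to the Reading 1 placebo effect at 80%), a non-significant interaction cannot be taken as support for independence. As written, the plan favours its own prediction. This should be fixed, but it does not call the design, the primary outcome or the enrolment target into question.

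**What to change.** Rewrite the Statistical Power paragraph in section F to give:

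1. the effect size, contrast and target power behind 104;
2. the power at 60 for that contrast, for the pooled placebo effect and for the interaction, with the dropout assumed;
3. the effects detectable with 80% power at 60 (about 0.74 SD for the pooled placebo effect and 1.47 SD for the interaction, before dropout).

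Keep the pollen-season reason. Declare one status before results are seen, either a pilot or a replication at the stated lower power, and make sections A to D and F agree.

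State that the interaction will be reported as an estimate with a 95% confidence interval, and that non-significance will not be read as proof that the placebo effect is independent of the information.

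No added enrolment is asked for. The cost is one rewritten paragraph, a stated power that may look less favourable, and a more cautious conclusion on the no-interaction hypothesis.

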**G. Subject Selection**

Participants were recruited from fliers in the local university and via social media.

Inclusion criteria:

1. Age between 18-60 years

2. Allergic rhinitis diagnosed by a physician

3. Taking medication against allergic rhinitis

Exclusion criteria:

1. Pregnancy

2. Diabetes

3. Psychiatric or neurological diseases

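### Entry is open to allergic rhinitis of any cause, but the primary model has no term for pollen allergy; recording it and adding it would be a cheap gain in precision of modest, uncertain size

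*Protocol*

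**What the plan says.** Section G sets three inclusion criteria: an age range, "Allergic rhinitis diagnosed by a physician", and current use of medication for it. None of them, and none of the exclusions, refers to the allergen, the season or current symptoms.

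Pollen appears in two other places. In Section E, one purpose of the control arms is "to assess general improvements of allergic symptoms due to changes in weather (pollen) conditions"; the other is to match time with the practitioner. In Section F, under Statistical Power, the protocol first says "we will need 104 participants for an alpha set at .05" and then explains the smaller target: "given that this is a pilot study and data collection is limited due to weather (pollen) conditions, we aim to include 60 patients".

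The primary analysis in Section F is an ANOVA on time, placebos and information. Section E describes randomization by sealed envelopes and names no stratification factor.

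**The concern.** By the protocol's own account, pollen conditions can change symptoms over the two weeks. A patient allergic to, say, house dust or animals is eligible but need not share that change. With two assessments, the placebo × time test is a comparison of change scores between arms, and the three-way test is the corresponding interaction. Both are judged against the spread of change within arms. If pollen-allergic and other patients differ in mean natural change, that difference widens the spread, and the stated model has nothing to absorb it.

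What is at stake is precision in a trial already planned below its own sample-size figure. The three-way test also bears on the hypothesis in Section D that information does not interact with the placebo effect, and extra noise there makes a non-significant result easier to obtain. An analysis plan written later could add a term only if allergen type had been recorded, and the protocol lists no such item.

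**Working it through.** **Inputs from the protocol.** Two-sided alpha .05 ("All tests will be two-tailed with alpha set at .05"); 104 participants needed; 60 planned in four groups.

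**Inputs the protocol does not give, so assumed.**
- Equal allocation: 15 per group, 30 v 30 for the placebo factor.
- Power behind 104: 80%, with 85 to 95% as a check.
- Share p of patients not pollen-allergic: 0.1 to 0.5.
- Difference k in mean two-week change between the two kinds of patient, in within-type SDs: 0.25 to 1.0.

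**Step 1: the protocol's figure.** The 104 cannot be reproduced, because Section F states neither the effect size nor the power. It can be solved backwards. For a 1-df effect in a four-group design, power comes from the noncentral F with 1 and N − 4 df and noncentrality f²N. Setting power to 80% at N = 104 gives f = 0.277, or d = 2f = 0.555. At N = 60 the noncentrality is 0.2774² × 60 = 4.62 and power is 56%.

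**Step 2: variance added by an unmodelled mix.** The variance of change is multiplied by V = 1 + p(1 − p)k², and the noncentrality is divided by V.

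| p | k | V | Power at 60, unadjusted | Difference from 56.0% |
|---|---|---|---|---|
| 0.1 | 0.25 | 1.006 | 55.8% | 0.2 |
| 0.2 | 0.5 | 1.040 | 54.4% | 1.6 |
| 0.3 | 0.5 | 1.052 | 53.9% | 2.1 |
| 0.3 | 0.8 | 1.134 | 50.9% | 5.1 |
| 0.3 | 1.0 | 1.210 | 48.4% | 7.6 |
| 0.5 | 1.0 | 1.250 | 47.2% | 8.8 |

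For p = 0.3 and k = 1: V = 1 + 0.3 × 0.7 × 1² = 1.21, and noncentrality is 4.62/1.21 = 3.82.

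**Step 3: the other reading of d.** The table takes d = 0.555 as free of the mix. If the earlier study had the same mix, d already contains that variance. The unadjusted power at 60 is then 56%, and adjustment raises the noncentrality. At p = 0.3, k = 1 it becomes 4.62 × 1.21 = 5.59, power 64%. At p = 0.3, k = 0.5 it becomes 4.62 × 1.0525 = 4.86, power 58%. On either reading the gain from adjusting is about 8 points at 1 SD and about 2 points at 0.5 SD.

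**Step 4: other values for the power behind 104.** With 85, 90 or 95%, f is 0.297, 0.321 or 0.357, and power at 60 is 62, 69 or 78%. Dividing the noncentrality by 1.21 gives 54, 60 or 70%, so the gain stays near 8 points.

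**Step 5: cost of the term.** Going from 56 to 55 error df at the same noncentrality changes power by less than 0.1 point. A chance correlation between the indicator and the arm adds on average about 1/59 = 1.7% to the variance of the placebo estimate. From the same calculation (V = 1.016 gives 55.4%), that is roughly 0.6 point. A useless indicator would therefore cost under 1 point, and the gains above are net of slightly less than stated.

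**The case against.** The strongest reply is that the text permits a mix but does not show that one will occur. Nearly all volunteers may be pollen-allergic, and then there is little to gain. Purpose, aim and hypothesis all speak of allergic rhinitis without qualification, so the entry criterion fits the stated target. Covariates are commonly left to an analysis plan. A yes/no indicator also removes only a constant mean difference: if pollen patients enrolled at different dates worsen and improve in turn, their mean change may differ little from that of the others. All of this stands, and it makes the point minor.

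A reader might infer four stronger things that the documents do not support.

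- *That the entry criterion contradicts the reason for 60.* Section F gives two reasons, and pilot status is independent of pollen. A season can also limit recruitment when most volunteers are seasonal.
- *That power falls short of the 104 calculation because of the mix.* The figure is "Based on effect sizes of our previous study", and Section B describes that study's patients simply as having allergic rhinitis. Its effect size may already carry the same variance.
- *That chance imbalance in allergen type is a second harm.* At p = 0.3 and k = 1 the SD of the difference in shares is √(2 × 0.21/30) = 0.118, shifting the estimate by 0.118 SD. The added variance of the 30 v 30 contrast is 2 × 0.21 × 1²/30 = 0.014, whose root is 0.118. It is the same quantity as the inflation in the table. With randomization and a concurrent control it is noise, not systematic bias.
- *That entry should be limited to pollen allergy.* That is a choice of scope, and it would narrow recruitment that the protocol already calls limited.

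**Conclusion.** The point holds as a cheap improvement of minor weight. Entry is wider than pollen-driven disease, the protocol regards pollen as a source of two-week change, and the named model has no term for whether a patient is pollen-allergic. If other patients are enrolled and change differently on average, both interaction tests lose precision without being biased.

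Across the assumed shares and differences, the gain from adjustment runs from about 0 to 9 points of power for the pooled placebo contrast. At a 30% share it is about 2 points for a 0.5 SD difference and about 8 points for 1 SD. These figures rest wholly on assumptions about the share, the difference and the power behind 104. On the same 80% basis, planning 60 instead of 104 costs 80 − 56 = 24 points, so this is a secondary matter.

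**What to change.** When the physician's diagnosis is checked at entry, record whether the patient is allergic to pollen (yes/no). In Section F, pre-specify this indicator and its product with time in the primary ANOVA; using it as a covariate for the change score is equivalent.

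The cost is one entry question and one degree of freedom, with no extra patients or visits. The gain will be small or nil if nearly all patients are pollen-allergic or if pollen patients' changes average out over the season. Fixing the term before the data are seen keeps its inclusion from depending on the results.

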**H. Possible Benefits**

Open placebos may or may not help the patients. The patient’s participation may help researchers develop more effective medications.

**I. Possible Risks**

Since no active treatment is being given and we ask the patients not to change the usual medications, there is a minimal risk to the patient.

**J. Data Location**

Study visits will be at the Medical School Berlin, Berlin, Germany.

**K. Data Security**

Data will kept in a locked room, with only researchers listed above have access to. Data will be treated according to the rules of the ethical committee which has approved this study.
